**FIGURE 2: EXPERIMENTAL DESIGN OF PUMPING ARTERIES**

Participants will be blinded to the order of the experimental interventions until arrival at the laboratory. All sessions will be conducted in the morning with each participant performing sessions at the same time of the day to minimize any potential diurnal variation. Participants will be instructed not to ingest any food or drink (except water) 4h before the sessions, and to avoid alcohol, caffeine, and vigorous exercise for at least 12h preceding each session [38].

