### **Design**

The study is constructed as a randomized, cross-over, repeated-measures intervention. Participants will attend 4, separate, intervention sessions consisting of one group class of Bike, Pump Power, Global Training or no exercise (CON). There will be a minimum of 72 h between sessions [18, 37], and each session will consist of initial rest, experimental intervention, and recovery (Figure 1). Participants will be advised not to engage in any strenuous physical activity at least 48 hours before the study days. Body composition and cardiorespiratory fitness for each participant will be evaluated prior to- and following to- the CON session, respectively.

|                           | WEEK 1 |   |   |   |   |   |   | WEEK 2 |   |   |   |   |   |   | WEEK 3 |   |    |    |    |    |    |
|---------------------------|--------|---|---|---|---|---|---|--------|---|---|---|---|---|---|--------|---|----|----|----|----|----|
|                           | 1      | 2 | 3 | 4 | 5 | 6 | 7 | 1      | 2 | 3 | 4 | 5 | 6 | 7 | 8      | 9 | 10 | 11 | 12 | 13 | 14 |
| ENROLLMENT         |        |   |   |   |   |   |   |        |   |   |   |   |   |   |        |   |    |    |    |    |    |
| Eligibility Screen        |        |   |   |   |   |   |   |        |   |   |   |   |   |   |        |   |    |    |    |    |    |
| Randomization             |        |   |   |   |   |   |   |        |   |   |   |   |   |   |        |   |    |    |    |    |    |
| Informed Consent          |        |   |   |   |   |   |   |        |   |   |   |   |   |   |        |   |    |    |    |    |    |
| INTERVENTIONS*     |        |   |   |   |   |   |   |        |   |   |   |   |   |   |        |   |    |    |    |    |    |
| Bike                      |        |   |   |   |   |   |   |        |   |   |   |   |   |   |        |   |    |    |    |    |    |
| Pump Power                |        |   |   |   |   |   |   |        |   |   |   |   |   |   |        |   |    |    |    |    |    |
| Global Training           |        |   |   |   |   |   |   |        |   |   |   |   |   |   |        |   |    |    |    |    |    |
| Control                   |        |   |   |   |   |   |   |        |   |   |   |   |   |   |        |   |    |    |    |    |    |
| ASSESSMENTS        |        |   |   |   |   |   |   |        |   |   |   |   |   |   |        |   |    |    |    |    |    |

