**FIGURE 1: TIMELINE AND MAIN OUTCOME VARIABLES OF PUMPING ARTERIES**

\* INTERVENTIONS WILL BE RANDOMIZED. THE TIMELINE HEREIN DISPLAYED IS MERELY A GRAPHIC REPRESENTATION OF A PARTICIPANT'S ACTIVITIES FOLLOWING RANDOMIZATION.

In each session, participants will initially undertake 20-min of supine rest on a cushioned examination table with resting energy expenditure measured by indirect calorimetry (K5, Cosmed, Rome, Italy) and heart rate and blood pressure recorded continuously using digital plethysmography technique (Finapres® Nova, Ohmeda, 2 Louisville, Colorado, USA), followed by regional assessments of PWV and pulse wave analysis of the aortic, brachial and femoral arteries on the right side of the body using applanation tonometry (Colson Analyze, ALAM Medical, Paris, France), and carotid arterial stiffness indices and wave intensity analysis using an ultrasound (Arietta V60, Hitachi Aloka Medical Ltd, Mitaka-shi, Tokyo, Japan). In the time following, participants will perform one of three exercise sessions (Bike, Pump Power or Global Training). Exercise sessions will consist of either a 45-minute class of Bike, Pump Power, and Global Training, while energy expenditure will be continuously measured by indirect calorimetry (K5, Cosmed, Rome, Italy) (Figure 2). These sessions are characterized by distinct metabolic demands, representing the typical sessions provided by gyms and health clubs to improve or maintain cardiovascular health. In the control condition, the participants will remain quietly seated for 45-min, maintaining a good posture. Only one participant will be tested per class with approximately 10-20 non-research participants also performing each group fitness class alongside the research participants. Upon completion of each intervention/session, participants will return immediately to the examination table and recover in the supine position for 30-min while hemodynamic and stiffness indices are reevaluated at 10, 20- and 30-min following recovery and compared to those at rest.

|                       | Rest |    | Exercise Session | Recovery |    |    |
|-----------------------|------|----|------------------|----------|----|----|
|                       | 15   | 20 | 45               | 10       | 20 | 30 |
| Advanced Hemodynamics |      |    |                  |          |    |    |
| Arterial Stiffness    |      |    |                  |          |    |    |

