### **Statistical Analysis and Data Monitorization**

Based upon a medium effect size of 0.154 derived from published changes in aortic PWV within-between modes of exercise [18], an a priori power analysis suggested that 22 participants are required to detect significant differences within-between groups, conditions and time points ( $1-\beta = 80\%$ ,  $\alpha = 0.05$ ). All data will be collated and/or analyzed using Microsoft Excel (v15.29.1, Microsoft Corporation, Redmond, Washington, United States) and Statistical Package for the Social Sciences version 24 (IBM, Armonk, New York, United States) software with results presented as mean  $\pm$  SD. Due to technical issues, missing data (~4–5%) may be evident during the study and subsequently should be replaced by averaging values before and after the missing value for the relevant variable prior to analysis.

Comparisons between interventions (Bike, Pump Power, Global Training and Control) over time (Rest vs. post-intervention time points) for indices of autonomic and vascular function will be examined via two-way

(intervention × time), repeated measures analysis of variance (ANOVA) and adjusted for sex and activity energy expenditure. Session differences for indices of autonomic and vascular function and energy expenditure will be analyzed using a one-way repeated measures ANOVA. Post-hoc comparisons will be conducted via Bonferroni's tests. Statistical significance will be set at  $p < 0.05$ .

The database will be stored in the GCP private server throughout the study period. The GCP lab will be responsible for management, storage and is the single user of the complete database.

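### Concealment of the session ends on arrival, before the Rest baseline is recorded, so knowledge of the coming session can enter the reference for every recovery value

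*Protocol*

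**What the plan says.** The text after Figure 2 states that "Participants will be blinded to the order of the experimental interventions until arrival at the laboratory". The Design section puts rest first in each session, then the intervention, then recovery. The text after Figure 1 gives the detail: "participants will initially undertake 20-min of supine rest on a cushioned examination table", with resting energy expenditure measured and "heart rate and blood pressure recorded continuously using digital plethysmography technique". The tonometry and carotid ultrasound measurements come next, and only then the class or the sitting. For Control, "In the control condition, the participants will remain quietly seated for 45-min".

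The Rest values are the reference. After the session, "hemodynamic and stiffness indices are reevaluated at 10, 20- and 30-min following recovery and compared to those at rest". The Statistical Analysis section compares the four interventions "over time (Rest vs. post-intervention time points) for indices of autonomic and vascular function" in a two-way repeated measures ANOVA.

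The Design section also attaches two assessments to one session only: "Body composition and cardiorespiratory fitness for each participant will be evaluated prior to- and following to- the CON session, respectively". The Cardiorespiratory Fitness section describes the second as an incremental cycle test to exhaustion.

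**The concern.** In a crossover analysed as change from Rest, the baseline should be a value that the assigned session cannot influence. Here the participant may lie through Rest already knowing what follows. The outcomes include heart rate, its variability, baroreflex sensitivity and pressure-dependent stiffness indices, all of which could plausibly respond to anticipation.

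Randomising the order balances effects of period. It does not balance a shift that belongs to the session, because that shift goes with the session to whatever position it is given. The analysis is adjusted for sex and activity energy expenditure, and neither term represents such a shift. At stake is whether a difference between sessions in change from Rest reflects recovery alone or partly a difference in the starting point.

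**Working it through.** **Sequence.** Set side by side, the sections give this order: arrival, when concealment ends (text after Figure 2); Rest recordings (Design; text after Figure 1); class or sitting; recovery at 10, 20 and 30 min, referred to Rest (text after Figure 1; Statistical Analysis). Nothing delays disclosure until Rest is complete. The exact minute of disclosure is not given, so this takes the sentence in its plain sense.

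**Effect on the contrast.** The plan gives no figure on this point, so there is none to reproduce. For session s let

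- change(s) = recovery(s) − Rest(s),
- d(s) = the shift in Rest(s) caused by knowing the session.

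For sessions A and B:

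observed contrast = true contrast − [d(A) − d(B)],

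and the same error appears at 10, 20 and 30 min, because all three use the same Rest value.

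**Illustration with assumed values** (the documents give none). Take a true class-minus-Control excess of 15 bpm in change from Rest.

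- Class shift 2 or 5 bpm, Control shift 0: 15 − 2 = 13; 15 − 5 = 10.
- Class shift 2 bpm, Control shift 5 bpm: 15 − (2 − 5) = 18. The error changes direction.
- Two classes, each shifted by 5 bpm: the error is 5 − 5 = 0.
- Two classes, shifted by 5 and 2 bpm: the error is 5 − 2 = 3 bpm.

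The sign of a contrast reverses only if the net shift exceeds the true contrast that remains at that time.

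**Effect on the test.** A simulation took one class against Control at one recovery time, with no true effect and only the class Rest value shifted, by b SD. Assumptions: total SD 1, within-person correlation 0.7, paired t-test, two-sided 5% level, 20,000 runs. The contrast is made of four readings, each with within-person variance 0.3, so its SD is √(4 × 0.3) = 1.095. The standard error is 1.095/√12 = 0.316 or 1.095/√22 = 0.234. Both sample sizes are shown because the Participants section gives 12 and the Statistical Analysis section gives 22.

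| b (SD) | False positives, n = 12 | False positives, n = 22 |
|---|---|---|
| 0 | 4.9% | 4.9% |
| 0.1 | 6% | 7% |
| 0.2 | 9% | 13% |
| 0.3 | 14% | 23% |
| 0.5 | 31% | 53% |

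The mean error equals −b throughout, to within simulation error. A larger sample does not reduce it and makes it more likely to be read as an effect. This is a simplified paired comparison, not the planned ANOVA, and b is in effect the net shift between the two sessions.

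**The case against.** The strongest reply is that nothing in the protocol shows that anticipation occurs. Participants are to be active adults used to both aerobic and resistance exercise, what awaits them is an ordinary commercial class, and they lie down for 20 minutes before the stiffness measurements. All of this may make the shift small. That stands: the text supports saying that knowledge can enter the baseline, not that it does.

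A reader might infer that the blind as written protects nothing. The documents do not support that. Concealment until arrival can also keep behaviour before the visit alike across sessions: the 48 h without strenuous activity, the 4 h fast, and the 12 h without alcohol, caffeine or vigorous exercise. The point is that concealment stops short of Rest, not that it is useless.

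A reader might also infer that the classes are necessarily understated against Control. That is not established either. The exhaustive cycle test follows Control. If it is on the same day, a participant told that it is the Control day may anticipate that test rather than sitting alone. The day grid in Figure 1 is blank in the text available, so same-day timing cannot be confirmed.

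The stated purpose is to compare the three classes, and a shift common to them cancels. This stands too, and leaves only unequal anticipation among the classes for that aim.

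Finally, Rest values can be compared across sessions in the planned analysis. With 12 participants that is a weak check, and it detects a difference without showing whether it came from anticipation or chance.

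**Conclusion.** The point holds as a weakness in the timing of disclosure: on the plain reading, the session is known before any Rest value is recorded, and all recovery values are referred to Rest. The resulting error in a between-session contrast is the difference between the two sessions' Rest shifts, the same at all three recovery times. That is an identity and needs no distributional assumption.

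The documents fix neither the size nor the direction of the shifts. The bpm figures and false-positive rates above rest on assumed shifts, and the rates also on the assumed correlation of 0.7. They show sensitivity, not a demonstrated bias. It would go too far to conclude that the results will be biased, or biased against the classes. This is a worthwhile improvement at little cost, better made in the design because the analysis cannot separate an anticipatory shift from other differences at Rest.

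**What to change.** Amend the sentence after Figure 2 to say that participants remain unaware of which session they will do until all Rest assessments of that visit are finished, and that the session is then disclosed, for example by opening a sealed card. In addition:

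- Give identical preparation and clothing instructions for all four visits, and have staff not name the session during Rest.
- Schedule body composition so that it cannot reveal Control before Rest, for example after the Rest assessments or at a visit not tied to Control. Without this, the card alone may not conceal the Control day.
- State that the fourth session can be inferred by elimination, so concealment can protect at most the first three.

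The cost is a few sentences in the protocol and a set of cards, with no extra measurement. Participants must come dressed for exercise on the Control day, and body composition may need minor rescheduling.

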## Intervention sessions

A lack of consistency with choreography, and other variables, such as the type of step, the level of impact of the step, arm movements and cadence of music, and intensity of a class will impact on the ability to use the results from previous research. Research involving pre-choreographed programs can control some of bias derived from the cadence of music, and intensity of a class by establishing identical music and choreography with instructors following strict guidelines and delivering the same choreography to the same music, thus standardizing class and exercise performance. While there is no specific mention of group classes in the American College of Sports Medicine (ACSM) Position Statement concerning Cardiorespiratory Fitness in apparently healthy adults [39], these appear to fulfil the criteria set down in the ACSM guidelines for enhancing and maintaining cardiovascular fitness.

The Bike session consists of a rhythmic indoor cycling class, with fluctuations in intensity set to changes in position, music rhythm, cadence, and revolutions per minute. It is an activity characterized by steps of workout with variable intensity and a high/moderate involvement of the cardiovascular system as well as the skeletal muscles [40]. Participants will be advised to strictly adhere to the verbal cues from the instructor when told to adjust cycling cadence and resistance. Pump Power is intended to provide a comprehensive total body weight-training program aiming to improve strength, muscular endurance and general fitness. The class is choreographed to music and uses a combination of barbells, body-weight exercises and free-weight plates. Participants select weights based on the target muscle group for the specific song or track and their own personal goals. The Global Training class encompasses both aerobic and resistance components, combining athletic movements like running, lunging and jumping with strength exercises such as barbells, body-weight exercises and free-weight plates. All classes will be 45 minutes long and contain 10-12 'tracks' or songs, each lasting from 4–7 minutes. The choreography of the music plays an important role because it may modify the participant's motivation and the intensity of the exercise. The classes start with an opening warm-up, followed by eight tracks, each targeting specific muscle groups, finishing with a static stretch cool down.

## Health-related Physical Fitness

### Body Composition

Height and sitting height will be measured to the nearest 0.1 cm and body weight will be measured to the nearest 0.1 kg on a scale with an attached stadiometer (model 770, Seca; Hamburg, Deutschland). Body mass index (BMI) will be calculated as body mass divided by height squared ( $\text{kg}\cdot\text{m}^{-2}$ ). Waist circumference

(WC), an estimate of the subcutaneous and intra-abdominal (i.e. visceral) adipose tissue in the abdominal region [41] will be measured to the nearest millimeter with an inelastic flexible metallic tape (Lufkin - W606PM, Vancouver, Canada) midway between the lower rib margin and the iliac crest.

Body composition will also be measured with a seca mBCA 515 using four pairs of electrodes (eight electrodes in total) that are positioned at each hand and foot. The 8-electrode technique enables segmental impedance measurement of the arms and legs. Impedance is measured with a current of 100  $\mu$ A at frequencies between 1 and 1 000 kHz. The mBCA 515 is designed for measurements in the standing position and consists of a platform with an integrated scale, a handrail system and a display and operation unit. Each side of the ascending handrail carries six electrodes of which two were chosen depending on person's height. According to the manufacturer's instructions, arms should be held straight.

All measurements will be performed at GCP by the same researcher at each measurement round.

### **Cardiorespiratory Fitness**

Each participant will perform a ramp incremental cycle ergometer test to exhaustion on a calibrated electronically braked cycle ergometer (Monark 839 E, Ergomedic; Monark, Vansbro, Sweden) at a pedal cadence of 70 to 75 rev.min using an electronically braked cycle ergometer. Initial and incremental workloads will be 30-40 W. The seat will be adjusted so that the participant's legs could be at near full extension during each pedal revolution.

Inspired and expired gases will be continuously analyzed, breath-by-breath, through a portable gas analyzer (K5, Cosmed, Rome, Italy). Before each test, the O2 and CO2 analyzers are calibrated using ambient air and standard calibration gases of known concentration (16.7% O2 and 5.7% CO2). The calibration of the turbine flowmeter of the K5 is performed using a 3-l syringe (Quinton Instruments, Seattle, Wash., USA) according to the manufacturer's instructions. Heart rate will be continuously monitored (Garmin, US). The participants will not carry the gas analyzer. This compact device is easy to attach without constricting the participants movements. Data will be evaluated in 10-second averages, and peak VO2 will be defined as the highest 10-second value attained in the last minute of effort provided 2 of the following criteria are met: (1) Attaining ~90% of age-predicted maximal heart rate; (2) Plateau in VO2 with an increase in workload (<2.0 mL.kg.min); (3) Rating of perceived exertion  $\geq$  18 (6-20) and; (4) Respiratory exchange ratio  $\geq$  1.1; (5) subjective judgment by the observer that the participant could no longer continue, even after encouragement.

All measurements will be performed at GCP by the same researcher at each measurement round.

### **Energy Expenditure**

The nature of group fitness classes presents several challenges for research aimed at measuring exercise-induced energy expenditure and hence the choice of both a valid and minimally invasive measuring device is critical for useable results. Therefore, expired gases at rest and during exercise will be continuously analyzed following thoroughly mixing prior to being sampled, through an open-circuit indirect calorimetry portable gas analyzer (K5, Cosmed, Rome, Italy) which has been previously validated [42]. Before each test, the O2 and CO2 analyzers will be calibrated using ambient air and standard calibration gases of known concentration (16% O2 and 5% CO2). Both the calibration of the flowmeter using a 3-l syringe (Quinton Instruments, Seattle, Wash., USA) and the scrubber calibration will be performed according to the manufacturer's instructions. Heart rate will be continuously monitored (Garmin, US). This compact device is easy to attach without constricting the participants movements. Data will be analyzed in 1-min averages.

## Advanced Hemodynamics

Individuals will be monitored non-invasively with a Finapres® Nova (Ohmeda, Louisville, Colorado, USA) (volume-clamp technique) in all measurement rounds. In supine humans, the finger arterial pressure signal can be modelled to a reconstructed pressure curve, using a general inverse anti-resonance model [43]. Subsequently, the device calculate left ventricular stroke volume (SV) and use this with HR to provide a calculated measure of CO. Based on reconstructed Q waveforms, the Windkessel model parameters (R, C and ZC) will then be assessed by the system [44]. Plethysmography sensors will be placed in the second and third finger of the right hand. An oscillometric cuff will then be attached to the same arm and the device calibration is completed. Heart rate signal (HR) will be computed from a I lead digitized electrocardiogram (ECG), included in the equipment. Individuals will be studied for 15 minutes.

## Effective Arterial Elastance

Effective arterial elastance is defined as a steady-state arterial parameter that incorporates the principal elements of vascular load. It can be calculated according published equations expression [45]:

$$Ea = \frac{R + Z_C}{T_S + RC \left(1 - e^{-\frac{T_D}{RC}}\right)}$$

where C is a compliance element that mimics the elastic and buffering properties of the large arteries, R is a resistive element that represents de resistance generated by the small arteries and arterioles, Zc is a second resistive element that represents the impedance of proximal aorta [46], and TS and TD are the systolic and diastolic periods, respectively. TS will be obtained as the time between the point before the abrupt rise of arterial pressure waveform and the dicrotic notch. Finally, ventricular end-systolic pressure (ESP) was approximated as:

$$ESP = SV.Ea$$

